**Outcome Measures:**

**Primary outcome**

- Completion of retinal screen (AI-DRS-System or screening by an ophthalmologist) within 3 months of enrollment and medical visit.

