**Secondary outcomes**

- Diabetic retinopathy diagnosis as determined by EyeArt or ophthalmologist
  - EyeArt-System results: normal, mtmDR, vtDR, or ungradable
  - Eye specialist referral clinical classification, using ICD-10 codes: E10.9, E11.9, E10.329, E11.329; E10.339, E11.339; E10.321, E11.321, E10.331, E11.331, E10.349, E11.349, E10.341, E11.341, E10.359, E11.359, E10.351, E11.351.
- Completion of retinal screen (AI-DRS-System or screening by an ophthalmologist) within 6 months of enrollment

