## STATISTICAL METHODS

**Sample Size and Power Calculations:** Based on historical data from participating SYH clinics, we determined that approximately 59% of patients completed diabetic retinopathy screening, we powered our study to detect an increase of at least 10% in retinopathy screening completion (59% in the standard of care group to 69% in the intervention group), and assuming an  $\alpha$  of 0.05 (significance) and a  $\beta$  of 0.8 (power), we estimated that the target enrollment to detect this difference is 722 participants (361 per arm) using a two independent sample Pearson  $\chi^2$  test. Accounting for up to 15% attrition from consent to study intervention (participants who agree to participate and consent via phone, and either do not keep their appointment or who at the clinic appointment decide to withdraw from the study), we estimated as many as 848 patients (424 per arm) would need to be enrolled to ensure adequate sample size. To assess secondary outcomes, we determined that among the patients who underwent retinal screening within the previous 12 months at the participating SYH clinics, 11% were diagnosed with diabetic retinopathy; therefore, based on a screening uptake increase of 10%, a corresponding 16% increase in diabetic retinopathy diagnosis is anticipated in the intervention arm. However, if after the initial refinement

phase of the project, it is determined that either a smaller or larger percent of the target population is currently completing DR screening, we will adjust the study enrollment accordingly, to ensure we will have sufficient statistical power to evaluate the anticipated 10% increase in screening uptake.

**Statistical significance and transformation of variables:** All statistical tests will be two-sided unless defined otherwise. Statistical significance will be set at  $p$ -value  $<0.05$ . Where distributional assumptions are necessary for the correct evaluation of statistical results, appropriate description, diagnostic evaluation, and (if required) transformation of variables will be carried out. In the event the parametric tests indicated are unable to be used, non-parametric versions will be used.

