| Evaluate the implementation and effectiveness of a multicomponent AI clinical intervention on DR screenings, early stages of DR detection, and referrals to the specialist for follow up on abnormal results. | 
 
1. Completion of DR screening. Data will be obtained through EHR at the time of the enrollment (baseline).
 
2. Results of the DR screening: for usual care specific diagnosis; for intervention group defined as normal, mild-to-moderate DR (mtmDR), visual threatening DR (vtDR) or ungradable. Data will be obtained through EHR at the time of the enrollment (baseline) and over the duration of the study.
 
3. Referral to specialist completion status and final diagnosis. Data will be obtained through EHR over the duration of the study.
 
 | 
To evaluate the effectiveness of the clinical intervention will be tested using a RCT (Aim 2), with the “intervention group”, which is characterized by 1) conducting autonomous DR screening system (H2.1) with 2) integration of the results into the EHR (H2.2). The “usual care” group represents the existing primary care model, which involves medical visits, referral to the specialist for a DR screening, and follow-up.
 
In addition, to evaluating the impact and efficiency of the POC-AI System we will also collect AI system data, number of orders submitted, screenings completed (images), number of ungradable and time of attempts, time the patient spent in front of the camera.
 |

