### 9.2 SAMPLE SIZE DETERMINATION

Sample size determination based on the primary outcome: Based on the hypothesis that SYHealth will see a minimum absolute screening increase of 10%, from 59% in the standard of care group to 69% in the intervention group of retinal screening uptake, and assuming an  $\alpha$  of 0.05 (significance), a  $\beta$  of 0.8 (power), the target enrollment for analysis is 772 participants (361 per arm). However, if after the initial refinement phase of the project it is determined that either a smaller or larger percent of the target population is currently completing DR screening we will adjust the study enrollment accordingly, to ensure we will have sufficient statistical power to evaluate the anticipated 10% increase in screening uptake. Assuming the screening rate of the target population will range from 45% to 65% (current estimate at 59%) the number of participants needed would range from 658 to 784 (current estimate 722). Anticipating up to a 10% attrition rate from consent to study intervention (participants who agree to participate and consent via phone, and either do not keep their appointment or who at the clinic appointment decide to withdraw from the study), we estimate the target enrollment will range from 732 to 872 (current estimate is 848 patients, 424 per arm) to ensure an analysis size of 722 participants (361 per arm) for a two independent sample Pearson chi2 test. Additionally, among the 2,514 patients who underwent retinal screening within the previous 12 months at the participating SYHealth clinics, 11% were diagnosed with DR; therefore, based on a screening uptake increase of 10%, a corresponding 16% increase in DR diagnosis (secondary outcome, H2.2) is anticipated in the intervention arm.

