#### 9.4.2 ANALYSIS OF THE PRIMARY EFFICACY ENDPOINT(S)

**Primary Endpoint: Increase in Retinal screening completion (H2.1)**

**Measurement:** Boolean variable (Yes/No) indicating completion of retinal screen within the defined study period (60 days from randomization).

**Scale:** Binary

**Analysis:** Chi-squared test or logistic regression will be used to compare screening completion rates between intervention and usual care groups. Regression covariates may include demographics and baseline clinical factors. Covariate selection will aim for a parsimonious model to achieve clarity and avoid overfitting. We will evaluate the intervention effectiveness across subgroups/categories by including a risk group classification variable in our models (to determine if there are differences in outcomes by group). If these risk groups are determined to confound the relationship between intervention and outcome, we will then stratify our analysis.

**Results Presentation:** Adjusted odds ratios with 95% confidence intervals will be reported.

**Assumption Checks:** When logistic regression is used, the data will be assessed for linearity, absence of multicollinearity, and influential outliers.

**Populations:** All enrolled participants will be included in the analysis.

**Missing Data:** Multiple deletion or imputation methods will be used to handle missing data depending on the pattern of missingness, e.g. if entire surveys are missing if missingness is driven by specific items or response groups in the survey, and/or if the data is missing completely at random. We have allowed for a 10% dropout/withdrawal rate between enrollment and intervention, and thus can use pairwise or listwise deletion of up to 10% of participants and still maintain adequate power for analysis.

**Outliers/Non-adherence:** Data outliers will be assessed to ensure they are not the result of data entry or measurement error. True data outliers will be handled either by trimming, adjusting the weight of the outliers, or by using robust regression techniques. Non-adherence will be addressed by analyzing data per-protocol in addition to intent to treat.

---

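### The SAP and the protocol give different time windows and starting points for the primary endpoint, and neither says which governs

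*Combined protocol and SAP*

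**What the plan says.** - **SAP, Outcome Measures, Primary outcome:** the screen must be completed "within 3 months of enrollment and medical visit". Completion "within 6 months of enrollment" is a secondary outcome.
- **Protocol 9.4.2:** the primary endpoint is a yes/no variable "indicating completion of retinal screen within the defined study period (60 days from randomization").
- **Protocol section 3, first primary endpoint:** "Completion of DR screening. Data will be obtained through EHR at the time of the enrollment (baseline"). No follow-up window is given there.
- **Protocol 4.4 and 6.1.1:** the intervention arm is imaged on the day of the study visit. Usual care is screened by an eye care provider on another day and elsewhere, with staff helping to book the appointment. A telehealth medical visit takes place on a later day than the screening.
- **SAP, Blinding:** study staff and data analysts are unblinded.
- **SAP, Sample Size and Power Calculations:** "Based on historical data from participating SYH clinics, we determined that approximately 59% of patients completed diabetic retinopathy screening". The design contrast is "59% in the standard of care group to 69% in the intervention group". No look-back period is attached to the 59%.

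**The concern.** The two documents can score the same participant differently, and the disagreement does not fall evenly on the arms. Few intervention screens should fall between day 61 and month 3, because imaging happens at the visit. Usual-care participants need a separate appointment, so some of theirs will. Choosing 60 days turns those exams into failures and widens the difference between arms.

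The trial is open-label with unblinded analysts, so a choice left open could be made with results by arm in view, and either choice could be defended by citing an approved document. The starting point is unsettled too: the SAP names two events, and the protocol names a third, randomization.

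The 59% planning rate raises a smaller question. Its period and population are not given, so it is not shown to describe usual care over either window, or in the patients actually enrolled, who must have gone at least 11 months without a retinal exam.

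**Working it through.** **1. The plan's own figure.** Inputs from the SAP: 59% against 69%, two-sided alpha 0.05, 80% power, 1:1 allocation, Pearson chi-squared test.

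n per arm = [1.960 × √(2 × 0.64 × 0.36) + 0.842 × √(0.59 × 0.41 + 0.69 × 0.31)]² / 0.10² = (1.330 + 0.568)² / 0.01 ≈ 360.5, rounded up to 361, so 722 in total. The stated figure reproduces exactly.

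**2. The two windows side by side.**

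| Usual-care exam date | SAP | Protocol 9.4.2 |
|---|---|---|
| up to day 60 | success | success |
| day 61 to month 3 | success | failure |
| after month 3 | failure | failure |

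Three months is 3 × 30.4 = about 91 days, so about 31 days are in dispute, roughly a third of the SAP window (31/91 = 34%).

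**3. Effect on the estimate.** Without any model:

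change in arm difference (60 days minus 3 months) = share of usual care screened in the disputed interval − share of intervention screened in it.

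The second term should be near zero by design. The first is not given anywhere. For scale, 18 such usual-care exams among 361 would be 18/361 = 5.0 points.

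**4. Illustration under an assumption.** Suppose a rate R applies at 12 months with a constant hazard, so completion by month m is 1 − (1 − R)^(m/12), with 60 days = 1.97 months. Neither the 12 months nor the constant hazard comes from the documents. The two values of R are the 59% planning rate and the 46% screening rate in the protocol synopsis.

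| R at 12 months (assumed) | 60 days | 3 months | Shift |
|---|---|---|---|
| 59% | 13.6% | 20.0% | 6.4 points |
| 46% | 9.6% | 14.3% | 4.7 points |

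**5. Does an uncertain control rate cost power?** Power for a fixed 10-point gain:

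| Control rate | N needed | Power, 361 per arm | Power, 424 per arm |
|---|---|---|---|
| 10% | 398 | 96.6% | 98.4% |
| 20% | 588 | 87.5% | 92.1% |
| 30% | 712 | 80.6% | 86.4% |
| 46% (worst case) | 784 | 76.8% | 83.1% |
| 59% | 722 | 80.1% | 86.0% |

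The control rate alone does little damage.

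**The case against.** The strongest reply is that the SAP is dated and explicit: one primary outcome at 3 months, with 6 months as secondary. This stands in part. Each document defines a single endpoint, so a reader who concludes that the trial has no primary result goes too far. But neither document gives the SAP precedence over 9.4.2.

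Four stronger readings are tempting and are not supported:

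- **Section 3 as a third window.** It says when data are obtained. Read as a window, it would put usual care near zero by design, since that arm is screened on another day. It is loose drafting that needs alignment.
- **The 59% as a 12-month rate.** The 12-month phrase in protocol 9.2, "among the 2,514 patients who underwent retinal screening within the previous 12 months at the participating SYHealth clinics", belongs to the 11% diagnosis rate. The synopsis's clinic counts give 24,000 × 13% + 9,000 × 14% = 4,380 patients with diabetes, and 2,514/4,380 = 57%. A 12-month origin is thus plausible, but it is an inference from rounded figures, and the synopsis also reports 46%.
- **The shift as half the target effect.** This mixes scenarios. With usual care at 13.6% to 20.0%, the gap to the planned 69% would be 49 to 55 points, and 5 to 6 points is about a tenth of that.
- **An underpowered trial.** Step 5 does not show it, and both documents already allow enrollment to be adjusted to the observed screening rate.

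Two further points stand. Scheduling help, education and care coordination could bring usual-care exams forward, so the true shift could be smaller or larger than the illustration. And the anchors diverge mainly for telehealth visits, because in-person medical visits share the study-visit day.

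**Conclusion.** The concern holds as a conflict between two current definitions of the primary endpoint, in both window and anchor, with no stated precedence. The likely direction is clear: 60 days gives a lower usual-care rate and a larger estimated effect than 3 months. That rests on the intervention arm being imaged at the visit, as the protocol plans. The size cannot be derived; about 5 to 6 points is an illustration under an assumed 12-month rate of 46% to 59% and a constant hazard. The documents do not show that the superiority conclusion would change.

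The period and population behind the 59% are unstated, which is a documentation gap. The sample size of 722 is correct for its inputs.

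**What to change.** Before any outcome data are analysed, issue a dated change to both documents:

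1. Use one sentence for the primary endpoint in the SAP, protocol section 3 and protocol 9.4.2. For example: retinal screen with an EHR exam date within 3 months of randomization (state the day number, such as day 90), counted identically in both arms. Another single window would also resolve the conflict if adopted in all three places.
2. Remove the medical visit as an anchor, since for telehealth it is a different date.
3. Reword section 3 so that the source and timing of data extraction cannot be read as the endpoint window.
4. Report the window not chosen as a labelled sensitivity analysis, and keep 6 months as secondary.
5. State the look-back period and the population behind the 59%, and whether it describes patients overdue for screening.

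The cost is wording in three places, a note on the source of the 59%, and one extra analysis. No extra participants, visits or procedures are needed.

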**Secondary outcomes**

- Diabetic retinopathy diagnosis as determined by EyeArt or ophthalmologist
  - EyeArt-System results: normal, mtmDR, vtDR, or ungradable
  - Eye specialist referral clinical classification, using ICD-10 codes: E10.9, E11.9, E10.329, E11.329; E10.339, E11.339; E10.321, E11.321, E10.331, E11.331, E10.349, E11.349, E10.341, E11.341, E10.359, E11.359, E10.351, E11.351.
- Completion of retinal screen (AI-DRS-System or screening by an ophthalmologist) within 6 months of enrollment

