**AI Algorithm and Performance:** The EyeArt AI system (EyeArt) has a clinically aligned framework and is trained on 375,000 images and validated on over 250,000 images. The system requires a digital fundus camera to capture two 45° field of view images, one centered on the optic disc and one centered on the macula. These images may be taken without dilation. EyeArt has been validated in a prospective, multicenter, pivotal clinical trial including 942 individuals with DM, where EyeArt demonstrated high accuracy against the Early Treatment Diabetic Retinopathy Study (ETDRS) reference standard clinical reference standard (mtmDR sensitivity: 96%, specificity: 88%, and vtDR sensitivity: 97%, specificity: 90%) by providing conclusive reports for >97% of eyes with reference standard while not requiring dilation for most. In a retrospective study of more than 100,000 consecutive encounters with people with DM, EyeArt also achieved a performance of 91.3% sensitivity and 91.1% specificity in detecting mtmDR. A subgroup analysis of participants in this clinical trial demonstrated that the sensitivity against the ETDRS reference standard for detection of mtmDR was significantly greater with EyeArt than with either an ophthalmologist dilated examination. Therefore, the FDA-cleared EyeArt is suitable for the prospective evaluation proposed in this application. The AI algorithms in EyeArt will be static (fixed) during the proposed evaluation process and will not be retrained. Therefore, no data requirements are associated with retraining the AI algorithms in EyeArt. Based on the existing EyeArt AI algorithm outcomes, SYHealth will implement a patient-centered model for its population of focus. In all four outcomes (mtmDR positive, vtDR positive), (mtmDR positive, vtDR negative), (mtmDR negative, vtDR negative), and ungradable, SYHealth's model will integrate a trained SYHealth clinical staff that will ensure patient care to proper follow up based on the EyeArt AI system results and as indicated by the primary care

provider. Preliminary Studies that guide the proposed AI System for autonomous DR screening are listed in **Appendix 3**.

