**The overall DRES-POCAI study will be considered complete** when participants' recruitment, all follow-up activities (including screenings and surveys) have been finalized, and the collected data has been cleaned, verified, and is ready for analysis. Participants assigned to the usual care group are anticipated to complete their participation within a six-month timeframe, and participants assigned to the intervention group are anticipated to complete the study's research activities at the 12 months from the initial study visit.

Participants may end their participation at any point of the intervention without completing the research activities in the following circumstances:

**Withdrawal:** Refers to participants who voluntarily decide to discontinue their involvement in the study before its completion.

**Lost to Follow-up:** Refers when participants fail to attend scheduled follow-up screenings, and /or are unreachable despite a defined number of contact attempts as defined in the protocols.

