2. **Diabetic retinopathy screening.** the screening will be conducted in a private office at each clinic study site (Chula Vista and King-Chavez) utilizing a Topcon TRC-NW400 Non-Mydriatic Retinal Camera that integrates an advanced, automated fundus camera capable of capturing true color images. It features a 360° rotating touch panel monitor, allowing the operator (staff) to capture images quickly and easily with a simple finger touch. The process also involves the EyeArt software, which is the first and only FDA-cleared AI technology capable of autonomous detection of both more than mild (mtm) and vision-threatening (vt) DR (**Appendix 3**). The EyeArt AI software will evaluate captured images to detect signs of DR within 60 seconds. Participants will receive the results as follows: normal, mtmDR, vtDR, or ungradable. The study staff will explain that the results of the screening are not the final diagnosis, and the results will be reviewed by their provider during the medical visit. The medical provider will review the results with the participant and discuss any recommended treatment plan, such as a referral to an eye specialist. Ultimately, it will be the participant's choice whether to proceed with additional tests or treatments to evaluate what was observed. The study staff will closely monitor the progress and follow up with participants with abnormal results. The results of the DR screening are also documented in participant's medical chart.

We are requesting a partial waiver of individual HIPAA authorization to review existing medical records in efforts to identify potential research subjects. The use of disclosure of PHI involves no more than minimal risk and granting the waiver will not adversely affect privacy rights and the welfare of the individuals whose records will be used. The random sample of patients from the participating clinics could not practicably be done without the waiver, as access to patient records will be necessary to provide the random sample. When potential subjects are approached to participate, they will be presented with the HIPAA research authorization (**Appendix 7**). PHI will not be re-used or disclosed for other purposes and whenever appropriate, the subjects will be provided with additional pertinent information after participation.

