#### 9.4.3 ANALYSIS OF THE SECONDARY ENDPOINT(S)

**Secondary Endpoint 1:** Early-stage DR diagnosis and treatment (H2.2)

**Measurement:** Diagnosis of DR.

**Scale:** Categorical (vtDR and mtmDR positive, vtDR negative and mtmDR positive, vtDR and mtmDR negative, ungradable).

**Analysis:** Chi-squared test or logistic regression will be used to compare screening completion rates between intervention and usual care groups. Regression covariates may include demographics and baseline clinical factors. Covariate selection will aim for a parsimonious model to achieve clarity and avoid overfitting. We will evaluate the intervention effectiveness across subgroups/categories by including a risk group classification variable in our models (to determine if there are differences in outcomes by group). If these risk groups are determined to confound the relationship between intervention and outcome, we will then stratify our analysis.

**Results Presentation:** Adjusted odds ratios with 95% confidence intervals will be reported.

**Assumption Checks:** When logistic regression is used, the data will be assessed for linearity, absence of multicollinearity, and influential outliers.

**Populations:** All enrolled participants will be included in the analysis.

**Missing Data:** Multiple deletion or imputation methods will be used to handle missing data depending on the pattern of missingness, e.g. if entire surveys are missing if missingness is driven by specific items or response groups in the survey, and/or if the data is missing completely at random. We have allowed for a 10% dropout/withdrawal rate between enrollment and intervention, and thus can use pairwise or listwise deletion of up to 10% of participants and still maintain adequate power for analysis.

**Outliers/Non-adherence:** Data outliers will be assessed to ensure they are not the result of data entry or measurement error. True data outliers will be handled either by trimming, adjusting the weight of the outliers, or by using robust regression techniques. Non-adherence will be addressed by analyzing data per-protocol in addition to intent to treat.

**Exploratory Endpoints:** Knowledge, Attitudes, Self-efficacy, and Patient Satisfaction (H2.3)

**Measurement:** Outcomes representing participant knowledge, attitudes, self-efficacy, and satisfaction with study participation.

**Scale:** Multiple outcomes will be explored and may include nominal, binary, or categorical data.

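### The secondary outcome defines a DR case differently in each arm and sets no time window, so a significant difference cannot by itself be read as more disease found

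*Combined protocol and SAP*

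**What the plan says.** The SAP (Secondary outcomes) defines the outcome as "Diabetic retinopathy diagnosis as determined by EyeArt or ophthalmologist". Beneath it are EyeArt categories for one source and a list of ICD-10 codes for the other. Protocol Section 3 assigns the sources by arm: "for usual care specific diagnosis; for intervention group defined as normal, mild-to-moderate DR (mtmDR), visual threatening DR (vtDR) or ungradable". Section 9.4.3 gives a single scale, made of EyeArt outputs only: "Categorical (vtDR and mtmDR positive, vtDR negative and mtmDR positive, vtDR and mtmDR negative, ungradable)". The SAP's General Approach compares the arms by logistic regression and counts missing results as no diagnosis.

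Protocol Section 8.1 says of the EyeArt result: "The study staff will explain that the results of the screening are not the final diagnosis". Section 2.3.3 says the same. Section 8.1 also describes EyeArt as detecting more-than-mild and vision-threatening DR, while Section 2.2 says that dilated exams can stage mild disease as well.

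On timing, Section 3 says of the DR results: "Data will be obtained through EHR at the time of the enrollment (baseline) and over the duration of the study". The SAP gives this outcome no window. Sections 4.4 and 6.1.1 add an EyeArt rescreen at one year for intervention participants whose first screen was negative.

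On the expected effect, Section 9.2 states that "a corresponding 16% increase in DR diagnosis (secondary outcome, H2.2) is anticipated in the intervention arm".

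**The concern.** H2.1 and H2.2 say that more screening will find more DR. To test that, a case must mean the same thing in both arms. Here one arm can contribute a machine-read screen result that the protocol itself calls non-final, and the other contributes a clinician's diagnosis. Nothing requires an EyeArt positive to be confirmed, says which source prevails when they disagree, or classifies an ungradable result.

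The disease thresholds differ too: more than mild in one arm, possibly any DR in the other. With no window stated, nothing excludes the one-year EyeArt rescreen, which only the intervention arm receives.

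The expected true gain is about one percentage point. Even a modest difference in case definition could exceed it, and a significant result could then be reported as more disease found.

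**Working it through.** **Inputs.** Completion 59% and 69%; 11% DR among those screened; 361 per arm; two-sided 0.05 (SAP, Sample Size; protocol 9.2). EyeArt accuracy (protocol 2.2): pivotal trial "mtmDR sensitivity: 96%, specificity: 88" per cent; retrospective study 91.3% and 91.1%.

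**The plan's own figures.** For 59% against 69%:

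n = [1.96·√(2·0.64·0.36) + 0.8416·√(0.59·0.41 + 0.69·0.31)]² / 0.10² = (1.330 + 0.568)² / 0.01 ≈ 361 per arm, which matches 722 in total.

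Expected DR diagnoses as a share of those randomized are 0.59·0.11 = 6.49% and 0.69·0.11 = 7.59%. That is a gain of 1.1 points, or 0.69/0.59 − 1 = 16.9% relative. The stated 16% is therefore a relative figure, apparently truncated.

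**No true difference.** Set completion at 59% and DR at 11% of those screened in both arms, and treat the clinical exam as error-free.

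- Usual care: 0.59·0.11 = 6.49%.
- EyeArt positives among those screened, at 96/88: 0.96·0.11 + 0.12·0.89 = 0.1056 + 0.1068 = 21.24%. Half are false (PPV 0.1056/0.2124 = 50%).
- Intervention arm: 0.59·0.2124 = 12.5%. The excess is 6.0 points: 6.3 from false positives less 0.3 from missed cases.
- At 91.3/91.1: 0.1004 + 0.0792 = 17.96%, so 0.59·0.1796 = 10.6%, an excess of 4.1 points.

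The chance of a significant intervention excess is Φ{[d − 1.96·√(2p̄q̄/n)] / √[(p₁q₁ + p₀q₀)/n]} with n = 361. For 12.5% against 6.5% this is Φ[(0.0604 − 0.0428)/0.0217] = Φ(0.81) = 79%. For 10.6% against 6.5% it is Φ(0.01) = 51%. A 20,000-replicate binomial simulation agreed to within about 0.01.

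**Allowing for mild DR.** Let m be the share of the 11% that is more than mild. The documents do not give m. Usual care counts all 11%. EyeArt positivity becomes sens·0.11m + (1 − spec)·(1 − 0.11m).

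| m | 96/88: arm rate | chance | 91.3/91.1: arm rate | chance |
|---|---|---|---|---|
| 100% | 12.5% | 79% | 10.6% | 51% |
| 75% | 11.2% | 60% | 9.3% | 28% |
| 50% | 9.8% | 37% | 7.9% | 11% |
| 25% | 8.4% | 17% | 6.6% | 3% |

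**Power for the real effect.** On one common standard with equal yield per screen, 6.49% against 7.59% has about 8% power at 361 per arm. About 8,490 per arm would be needed for 80%.

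**Counting confirmed diagnoses only.** Let c be the share of true EyeArt positives whose diagnosis is confirmed and returned. The documents do not give c. At 59% and 69% completion and 96% sensitivity, the comparison is 0.69·0.11·0.96·c = 7.29%·c against 6.49%.

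- At c = 100% the gain is 0.8 points, not 1.1.
- The sign reverses below c = 6.49/7.29 = 89%.
- At c = 75% it is 5.5% against 6.5%.
- At c = 50% it is 3.6% against 6.5%.

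Under a common more-than-mild threshold, m multiplies both sides and cancels, so the 89% does not depend on it.

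**The case against.** A reader might infer that a significant result would be spurious. The documents do not support that.

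- **Mild DR works the other way.** It can count in usual care but lies below EyeArt's threshold. If most of the 11% is mild and specificity is 91.1%, the net bias almost disappears, as the table shows. However, two opposing arm-dependent biases of unknown size still do not give an interpretable comparison.
- **The clinical exam is not error-free.** Protocol Section 2.2 reports higher EyeArt sensitivity for more-than-mild DR than an ophthalmologist's dilated exam, against the ETDRS reference standard. Part of an excess could be real disease that usual care misses. In the other direction, Section 2.2 does not say whether 88% is per eye or per patient; if per eye, the patient-level false-positive rate would be higher.

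A reader might also infer that the arms have unequal follow-up for this outcome. Section 4.4 does say "Participants assigned to the usual care group are anticipated to complete their participation within a six-month timeframe", and gives 12 months for the intervention arm. But that describes participation, not the period of record extraction, and the Synopsis gives a participant duration of one year without separating the arms. No text says that the one-year rescreen counts. What stands is that no window is stated and nothing excludes the rescreen. The false-positive result does not depend on this.

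The SAP does list ICD-10 codes for specialist results, so it is not confined to the scale in 9.4.3. It does not map the two sets onto one case definition.

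The most serious objection is to the obvious remedy. Usual care reaches a diagnosis at one exam. The intervention arm would need an EyeArt positive, a completed referral and a returned result. The SAP's Exploratory analysis paragraph concedes that specialist results will exist only for some intervention participants with abnormal or ungradable screens. Confirmed diagnosis as the sole definition could therefore make the arm that finds more disease look worse. That objection stands, and the fix has to allow for it.

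**Conclusion.** The point holds in this form. The case definition differs between arms in source, confirmation and threshold, and no time window is set. At the documents' own accuracy figures, with equal completion, 11% DR and an error-free clinical exam, AI false positives alone can give a 51% to 79% chance of a significant excess if all of the 11% is more than mild. That range falls to 28–60%, 11–37% or 3–17% if 75%, 50% or 25% of it is. So the artefact can occur, but its size is uncertain. It should be judged against a planned true gain of 1.1 points with about 8% power. A significant difference on this outcome cannot by itself be read as more disease found. Screening completion, the primary outcome, is not affected.

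**What to change.** 1. **One threshold.** Define a case in both arms as more-than-mild DR. State which of the listed ICD-10 codes meet it, and replace the EyeArt-only scale in Section 9.4.3.
2. **One window.** Use 6 months from randomization, with all randomized participants in the denominator. Exclude the one-year EyeArt rescreen from between-arm comparisons.
3. **Two results side by side.** Report provider-confirmed DR in both arms, using the final diagnosis in the health record, and screen-positive or diagnosed DR as now defined. Add the share of EyeArt positives that completed referral and the share confirmed. Claim increased DR diagnosis only from confirmed diagnoses.
4. **Declare the opposite bias.** State that the confirmed comparison works against the intervention when referral is incomplete, with the sign reversing below about 89% confirmation on the planning figures. Give a sensitivity analysis over the confirmation share, or one using the predictive value observed among referred positives.
5. **Restate the expected effect.** Replace the 16% increase with about 17% relative, 6.5% to 7.6% (1.1 points, assuming an 11% yield per screen in both arms), and about 8% power at 361 per arm. Restricting to more-than-mild DR makes the absolute gain and the power smaller still.

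**Cost.** Wording changes in the SAP and protocol, and a little more analysis. Section 3 already collects referral completion and final diagnosis, although specialist results will be incomplete in the intervention arm. The secondary result is likely to be less favourable or less definitive.
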